## Abstract

**Background:**

Irritable Bowel Syndrome (IBS) is a common gastro-intestinal disorder in primary and secondary care, characterised by abdominal pain, discomfort, altered bowel habits and/or symptoms of bloating and distension. In general the efficacy of drug therapies is poor. Hypnotherapy as well as Cognitive Behaviour Therapy and short Psychodynamic Therapy appear to be useful options for patients with refractory IBS in secondary care and are cost-effective, but the evidence is still limited. The IMAGINE-study is therefore designed to assess the overall benefit of hypnotherapy in IBS as well as comparing the efficacy of individual versus group hypnotherapy in treating this condition.

**Methods/Design:**

The design is a randomised placebo-controlled trial. The study group consists of 354 primary care and secondary care patients (aged 18-65) with IBS (Rome-III criteria). Patients will be randomly allocated to either 6 sessions of individual hypnotherapy, 6 sessions of group hypnotherapy or 6 sessions of educational supportive therapy in a group (placebo), with a follow up of 9 months post treatment for all patients. Ten hospitals and four primary care psychological practices in different parts of The Netherlands will collaborate in this study. The primary efficacy parameter is the responder rate for adequate relief of IBS symptoms. Secondary efficacy parameters are changes in the IBS symptom severity, quality of life, cognitions, psychological complaints, self-efficacy as well as direct and indirect costs of the condition. Hypnotherapy is expected to be more effective than the control therapy, and group hypnotherapy is expected not to be inferior to individual hypnotherapy.

**Discussion:**

If hypnotherapy is effective and if there is no difference in efficacy between individual and group hypnotherapy, this group form of treatment could be offered to more IBS patients, at lower costs.

**Trial registration number:**

ISRCTN: ISRCTN22888906

## Background

Irritable bowel syndrome (IBS) is a chronic functional gastrointestinal disorder, characterised by recurrent episodes of abdominal pain, discomfort, altered bowel habits and/or symptoms of bloating and distension, not explained by structural or biochemical abnormalities [1]. The estimated prevalence is 14-24% for women and 5-19% for men [2]. The consultation rate is relatively low: only 20-25% of IBS patients seek medical advice [3] but because the prevalence is so high this still represents a substantial number of patients. The reported incidence of IBS in primary care is 4-13/1000 patients a year [4]. General Practitioners see on average 1-2 new IBS patients a week. In the Netherlands about 10% of the patients seen by a GP are referred to a medical specialist, i.e. gastroenterologists [5], in UK 44% [1]. The estimated number of patients, who are diagnosed with IBS after referral to the gastroenterologists, varies from 20-70% [6]. Patients with IBS can have severe and often incapacitating complaints, resulting in as much annual absence from work as, for instance, from the flu [7]. The diagnosis can only be considered if there are no other indications of organic pathology and there are now consensus based criteria, the most recent of which are the so called Rome III criteria [8]:

### Irritable Bowel Syndrome

#### Diagnostic criterion*

Recurrent abdominal pain or discomfort** at least 3 days/month in the last 3 months associated with *two or more *of the following:

Improvement with defecation

Onset associated with a change in frequency of stool

Onset associated with a change in form (appearance) of stool

* Criterion fulfilled for the last 3 months with symptom onset at least 6 months prior to diagnosis

** "Discomfort" means an uncomfortable sensation not described as pain.

In pathophysiology research and clinical trials, a pain/discomfort frequency of at least 2 days a week during screening evaluation is recommended for subject eligibility

Three types of IBS can be distinguished: IBS with either predominant constipation, predominant diarrhoea, or alternating periods of diarrhoea and constipation. Several pathophysiological mechanisms underlying IBS have been proposed, including a disturbance in intestinal motility and enhanced visceral sensitivity which, according to the bio-psycho-social model of IBS, interact with other factors such as environmental influences, parent-child interactions and disturbed stress responses to result in symptoms [9].

Effective therapy of IBS is lacking. A recent review on pharmacological treatment for IBS [10] concluded that in general the efficacy of drug therapies is poor. Bulking agents, antispasmodics, and antidepressants can be tried but the response is often suboptimal.

Since 1984 [11] there has been an increasing research interest on the effectiveness of psychological treatment for IBS. A wide range of psychotherapeutic interventions have been studied including: relaxation therapy, biofeedback, cognitive behavioural therapy (CBT), short psychodynamic therapy and hypnotherapy. Two Cochrane reviews on the efficacy of hypnotherapy [2] and other psychological therapies [12] support effectiveness. In England the NICE guideline (2008) on IBS was published, with a special section on the psychological interventions which concluded that "CBT as well as short Psychodynamic and Hypnotherapy can be a useful option for patients with refractory IBS" [13]. Hypnosis is officially recognised as a legitimate medical treatment by the British Medical Association (1955) and the American Medical Association (1958). There has been much research on the use of hypnosis in the treatment of (chronic) pain [14] and, as pain is the main symptom of IBS, it is understandable that therapists have applied hypnosis in treatment of IBS patients. Pooled results of research about the effectiveness of hypnotherapy for IBS-patients are described in three reviews/meta-analysis. The NICE guideline [13] concludes that hypnotherapy may be considered a promising intervention for IBS, but judges the evidence as still too limited. Further investigation is recommended, with special interest in the potential of this intervention as a primary care therapy option, with long term follow-up. The Cochrane review on hypnotherapy for treatment of IBS concludes that "The quality of the included trials was inadequate to allow any conclusion about the efficacy of hypnotherapy for irritable bowel syndrome." And, "More research with high quality trials is needed" [2].

In a more recent meta-analysis Ford et al. conclude that hypnotherapy leads to less persistence of complaints than usual care or control therapy [15].

On the basis of these publications one can conclude that hypnotherapy is a promising and possibly cost-effective intervention for IBS in secondary care. Further investigation with high quality trials and long term follow up is needed, especially with regard to its efficacy in a primary care setting.

To improve cost effectiveness, group application of hypnotherapy could be considered. So far, there has only been one study on a group application [16], indicating no significant difference in effectiveness in a population of only 33 patients.

We have designed a RCT, comparing the effectiveness and costs of individual and group hypnotherapy with a control intervention in patients with IBS. In this paper, we describe the aim, design and methodological challenges of the study protocol.

## Methods/Design

### Aims

The primary objectives of this study are two-fold. The first aim is to assess the efficacy of hypnotherapy in IBS treatment. The second goal is to compare the efficacy of group hypnotherapy with individual hypnotherapy in IBS treatment. Secondary objectives are to assess the effect of individual or group hypnotherapy on symptom severity, on quality of life, dysfunctional cognitions, psychological complaints, self-efficacy, and IBS related costs.

### Design

The study is designed as a comparative and a non-inferiority 12-weeks single blind controlled parallel-group trial. The trial will involve IBS patients in primary and secondary care, who will be randomly allocated to either 6 sessions of individual hypnotherapy, 6 sessions of hypnotherapy in group format, or 6 sessions of educational supportive therapy in a group format (control condition) (Flowchart Figure 1). Starting May 2011, the inclusion of patients will take approximately two years, with a follow-up of nine months.

**Figure 1 F1:**
[figure not shown]
**Design of the RCT**.

### Ethical considerations

The study is conducted according to the principles of the Declaration of Helsinki and in accordance with the Medical Research Involving Human Subjects Act (WMO). The study protocol has been approved by the Medical Ethics Committee of the University Medical Centre of Utrecht, the Netherlands.

Patient data will be coded and analysing and publication of the results will be anonymous.

### Hypotheses

The primary hypotheses assessed in this study are:

At the end of therapy, more patients in the hypnotherapy condition will report adequate relief than in the educational supportive therapy condition (control treatment).

Hypnotherapy offered in a group format is as effective as individual hypnotherapy.

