#### Main study parameter/endpoint

In line with previous conclusions on optimal outcome assessment in trials on functional gastrointestinal disease [23,24], we chose the number of weeks with adequate symptom relief as the primary outcome. This measure addresses weekly symptom improvement in IBS with treatment using a single question ("Did you have adequate relief of IBS-related abdominal pain or discomfort in the past week?") scored on a dichotomous scale (Yes/No). This instrument is a well validated simple outcome assessment for IBS treatment [25] with a positive responder being defined as someone with more than 2 weeks adequate relief per month [26] which has determined to indicate a clinically significant improvement [26].

The first primary outcome is the difference in the percentage of positive responders between group hypnotherapy and group educational therapy. Group hypnotherapy is expected to be substantially more effective than educational therapy.

The second primary outcome is the difference in percentage of positive responders between group hypnotherapy and individual hypnotherapy. Group hypnotherapy is expected not to be inferior to individual hypnotherapy.

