### Sample Size Calculation

Assuming an individual hypnotherapy response rate of 57% [2], a maximum acceptable level of difference of 15% between individual and group hypnotherapy, an alpha of 0.05 and power (1-beta) of 0.80, 135 patients are required in both arms of the non-inferiority trial to show that group-hypnotherapy is not inferior to individual hypnotherapy.

Spiller [34], in an overview of 25 randomised controlled trials, states that when the placebo response is plotted against the length of study, placebo response will be maximum of 75% at around 6-8 weeks, falling to 25% at 24 weeks and zero at 12 months. Our follow-up period will be 9 months. To test whether group hypnotherapy is more effective than group placebo therapy, we will have more than sufficient power assuming a placebo-response rate of 25% and a group hypnotherapy response rate of 57% [13] using the proposed 135 patients in both arms. Powering the study for only the comparison between hypnotherapy and the control intervention, would require only 44 patients in both arms assuming an alpha of 0.05, a power (1-beta) of 0.80, a cluster size of 6 patients per therapist and an intra-class correlation coefficient of 0.05. Assuming at least 10% of loss to follow-up, 354 patients need to be included in the study (150+150+54 (placebo-arm)).

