#### Uni- & bivariate analysis

The percentage of patients with a positive response will be calculated post-treatment and at 9 months after treatment and differences between the three randomisation arms will be tested with the chi-square test.

In addition, the adequate relief scores and secondary outcomes (IBS- SSS, IBS-QoL, SCL-90-, CS- FBD-, SES- and TiC-P scores) will be estimated by time point of assessment and arm of randomisation using a statistical model for repeated measurements (preferably a random effects model). To assess the difference between the arms of randomisation by time point of assessment, terms for interaction of {arm × time point} will be included in the statistical model.

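### The first primary comparison is stated with conflicting contrasts and no settled time point, and the control rate behind its power is argued from later follow-up than the end of therapy

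*Protocol article*

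**What the plan says.** **Contrast.** Under Aims: "The first aim is to assess the efficacy of hypnotherapy in IBS treatment". The first primary hypothesis (Hypotheses) is equally general: "At the end of therapy, more patients in the hypnotherapy condition will report adequate relief than in the educational supportive therapy condition". The endpoint section narrows it: "The first primary outcome is the difference in the percentage of positive responders between group hypnotherapy and group educational therapy". The Sample Size Calculation follows the narrow version: "To test whether group hypnotherapy is more effective than group placebo therapy". The analysis section (Uni- & bivariate analysis) names neither contrast: "differences between the three randomisation arms will be tested with the chi-square test".

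**Time.** Only the first hypothesis carries a time, the end of therapy. The endpoint section gives none, and the non-inferiority hypothesis has none. Time line and follow-up has adequate relief recorded weekly for four weeks after treatment and again for four weeks at 9 months. In the analysis section the responder percentages "will be calculated post-treatment and at 9 months after treatment", with no ranking of the two.

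**Control rate.** The Sample Size Calculation cites a placebo response of up to 75% at 6-8 weeks, 25% at 24 weeks and zero at 12 months. It then continues "Our follow-up period will be 9 months. To test whether group hypnotherapy is more effective than group placebo therapy" and assumes 25% on control against 57% on group hypnotherapy. The Placebo effect section quotes two other rates from drug and fibre trials: a median of 47% and a pooled 37.5%.

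**The concern.** Three sections describe the same primary test in three ways: hypnotherapy in general against control, group hypnotherapy against control, and a test across all three arms. These can give different answers. A three-arm test can reject because the two hypnotherapy formats differ. A pooled contrast can succeed on the strength of the individual format alone. Whoever analyses the trial would have to choose, and nothing printed stops that choice being made after the data are seen.

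The time point has a second consequence. The hypothesis is set at the end of therapy, while the control rate that makes the comparison look amply powered is argued from later follow-up. If the control response just after a 12-week attention-matched programme is nearer the other rates the article quotes, the small control arm (54 randomised) may not support the first primary claim.

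**Working it through.** **1. Side by side**

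| Section | Contrast | Time |
|---|---|---|
| Aims | hypnotherapy, no format | none |
| Hypotheses (first) | hypnotherapy, no format, v education | end of therapy |
| Main study parameter/endpoint | group hypnotherapy v group education | none |
| Sample Size Calculation | group hypnotherapy v group placebo | control rate argued from placebo decline and 9-month follow-up |
| Uni- & bivariate analysis | three arms, chi-square | post-treatment and 9 months, unranked |

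On the cited decline, 25% belongs to week 24. The two measurement windows are weeks 12 to 16 and weeks 52 to 56 (Table 1), so 25% is the cited value for neither.

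**2. The plan's own figures**

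- Non-inferiority, 57% in both arms, margin 15 points, one-sided 0.05, power 0.80: n = 2 × 0.57 × 0.43 × (1.645 + 0.842)² / 0.15² = 134.7, so 135. This matches.
- Superiority, 25% v 57%, two-sided 0.05, power 0.80, mean rate 0.41: n = [1.96 × √(2 × 0.41 × 0.59) + 0.842 × √(0.25 × 0.75 + 0.57 × 0.43)]² / 0.32² = 35.9.
- Design effect for clusters of 6 and ICC 0.05: 1 + 5 × 0.05 = 1.25. Then 35.9 × 1.25 = 44.9, against 44 stated.
- Loss of 10%: 135 / 0.9 = 150, and 54 × 0.9 = 48.6 evaluable controls.

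**3. Power of group v control by control rate**

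Effective sizes are 135 / 1.25 = 108 and 48.6 / 1.25 = 38.9. Power = Φ[(0.57 − p − 1.96 × SE0) / SE1], where p is the control rate, SE0 the pooled and SE1 the unpooled standard error.

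- p = 25%: (0.32 − 1.96 × 0.0935) / 0.0842 = 1.62, power 95%.
- p = 37.5%: (0.195 − 1.96 × 0.0935) / 0.0911 = 0.13, power 55%.
- p = 47%: (0.10 − 1.96 × 0.0932) / 0.0931 = −0.89, power 19%.

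With 44 controls these become 93%, 52% and 18%. For pooled hypnotherapy (effective 108 + 135 = 243) against 48.6 controls, with the design effect in the group-format arms only, power is 98%, 62% and 21%. The contrast therefore moves power by about 2 to 7 points, and the control rate moves it by tens of points.

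**4. Chance of a false claim of benefit**

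I simulated normal test statistics with no true effect, 135 / 135 / 49 patients, and each test at two-sided 5% (2.5% in favour of hypnotherapy). The correlation of the group-only and pooled contrasts at one time is √[(1/270 + 1/49) / (1/135 + 1/49)] = 0.93. The between-time correlation is assumed to be 0.3 or 0.5.

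- One test: 2.5%.
- Either contrast, one time: 3.3%.
- One contrast, either time: about 4.5 to 4.8%.
- Either contrast, either time: 6.3% (correlation 0.3) or 6.0% (correlation 0.5).

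**The case against.** The case for the plan is that it is less loose than it looks. Only one time is ever attached to a primary hypothesis, the end of therapy. Later follow-up is said to serve the durability of effects, and analysing a second time contradicts nothing. That stands: a reader might infer that 9 months is a rival primary time, but no section says so. What remains is that the control rate is not argued for the time the hypothesis names.

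Four further inferences are tempting and are not supported.

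- *A false-positive rate of about 12%.* That is the two-sided figure for any of four tests and includes results showing hypnotherapy to be worse. For a false claim of benefit the figure is about 6%. Even that needs an any-of-four rule which the article does not state, so it measures the room left open, not a planned error rate.
- *Non-inferiority cut loose from superiority over control.* A formal testing order is commonly left to an analysis plan, which is not shown here. The abstract's Discussion already makes the group-format conclusion depend on hypnotherapy being effective as well as on no difference between formats.
- *A margin that admits a placebo-level treatment.* 57% − 15% = 42% is below 47%, but 47% is the median of the drug and fibre trials. 42% is above both 37.5% and the assumed 25%, and the trial has its own control arm.
- *Two different primary variables.* The endpoint section does say "we chose the number of weeks with adequate symptom relief as the primary outcome". It then builds the responder definition from those weeks and states both primary outcomes as responder percentages. The abstract agrees.

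**Conclusion.** The point holds for the contrast and the time of the first primary test, and for the control rate tied to that time. The printed sections contradict each other on the contrast, and an unseen analysis plan would have to overrule at least one of them.

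The multiplicity effect is modest: about 6% against 2.5%, and only if any of the four versions could be claimed. The power effect is larger: about 95%, 55% and 19% at control rates of 25%, 37.5% and 47%. These figures assume 57% on group hypnotherapy, a two-sided 5% test, 48.6 evaluable controls and a design effect of 1.25 in the group-format arms. The 37.5% and 47% are trial averages quoted in the article for other treatments. They serve as a range and are not the expected rate for this control programme. This is an error of wording that should be corrected. It is not evidence that the design cannot work.

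**What to change.** - **Hypotheses:** reword the first hypothesis to match the endpoint section: responder percentage, group hypnotherapy against group education, in the four weeks after treatment. Give the non-inferiority hypothesis the same time point.
- **Uni- & bivariate analysis:** name a two-group test of that contrast as the first primary test. List as secondary the 9-month results, pooled hypnotherapy, individual hypnotherapy against control, and the three-arm chi-square test.
- **Sample Size Calculation:** justify the control rate for the four weeks after treatment, or restate power over the range of rates the article quotes.

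The cost is a few sentences, with no change to data collection and no split of alpha. The downside is that the stated power for the first primary comparison may look less favourable once the control rate is tied to the end of therapy.

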### Study population

The study population consists of patients with IBS referred by GP or medical specialist. Ten general hospitals and four psychological practices in primary care collaborate in the study.

#### Inclusion criteria

Age 18-65 years

diagnosis of IBS according to the Rome III criteria. The Dutch translated version of the IBS Module of the Rome Foundation [8] is used to check criteria.

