### Outcome assessment

As no objective standards for diagnosing functional GI-diseases exist, outcome assessments have to be based on subjective criteria. According to Irvine [23] the "adequate relief" questionnaire [25] is the current standard primary outcome measurement in treatment trials of Functional Gastrointestinal Disorders. For a more detailed IBS symptom assessment the IBS-Severity Scoring System [27] is recommended [24]. Furthermore, IBS related Quality of Life is an important secondary outcome measure [23]. At present, the IBS-Quality of Life measurement [28] is the best choice, "because it has been the most extensively validated and shows appropriate psychometric quality" [24]. Mangel, (outcome measure:"adequate relief "[25]) and [name] (IBS-SSS [27]) gave their consent for translating these questionnaires into Dutch.

IBS-complaints can have an episodic course and in accord with the recommendation on measuring severity during episodic symptoms by the research design of the Rome committee [23], patients will fill in the assessments on two occasions: immediately at the end of treatment and after nine months. Also the 'adequate relief' question is asked every week, for a period of four weeks.

It is possible that the patients in the control group with educational supportive therapy also will experience some improvement in their complaints, but the expectation is that treatment with hypnotherapy will be superior.

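### Adequate relief is not asked before treatment and entry needs pain on only 3 days a month, so entrants who already meet the responder definition could dilute the comparisons, chiefly non-inferiority

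*Protocol article*

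**What the plan says.** **Entry.** Under Inclusion criteria, the only conditions are age 18-65 and a "diagnosis of IBS according to the Rome III criteria. The Dutch translated version of the IBS Module of the Rome Foundation [8] is used to" verify it. The Diagnostic criterion subsection of the Background gives the Rome III requirement as pain or discomfort "at least 3 days/month in the last 3 months associated with" two or more bowel features. The same subsection adds: "In pathophysiology research and clinical trials, a pain/discomfort frequency of at least 2 days a week during screening evaluation is recommended for subject eligibility". Neither Inclusion criteria, Exclusion criteria nor Procedure takes up that threshold or any severity cut-off.

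**Endpoint.** Main study parameter/endpoint uses one weekly yes/no item, "Did you have adequate relief of IBS-related abdominal pain or discomfort in the past week", "with a positive responder being defined as someone with more than 2 weeks adequate relief per month". With four weekly answers, that means at least 3 of 4.

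**Timing.** Time line and follow-up schedules this item for the four weeks after treatment and for four weeks at 9 months. Table 1 has no adequate-relief mark at week 0, although the IBS module, IBS-SSS, IBS-QOL, SCL-90, CS-FBD, SES and TiC-P are all taken then.

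**Context.** Outcome assessment, in the Discussion, accepts that "IBS-complaints can have an episodic course". Other treatments during the study lets patients continue their usual care.

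**The concern.** The primary endpoint is a state after treatment, not a change from entry. A patient whose three qualifying days fall in a single week of the month is eligible and has three weeks without pain. If that patient answers yes in those weeks, the responder definition is met with no help from the trial treatment. The same holds for a patient who already has adequate relief on continued usual care.

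Randomisation spreads such patients evenly, so they cause no imbalance between arms. They do add the same expected proportion of responders to each arm, which narrows any true difference. In the superiority comparison this costs power. In the non-inferiority comparison it works towards the conclusion the trial hopes to reach. Without a baseline answer to the relief question, the final report could not show how many such patients there were.

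**Working it through.** **1. The plan's own figure.** Inputs from Sample Size Calculation: response 57% in both hypnotherapy arms, margin 15 points, alpha 0.05, power 0.80.

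n = (1.645 + 0.842)² × 2 × 0.57 × 0.43 / 0.15² = 134.7, so 135 per arm. This matches the plan and shows that alpha is one-sided (one-sided 0.025 would give 172). With 10% loss, 135/0.9 = 150.

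**2. Dilution model.** Let f be the share of enrolled patients who would be responders in any arm. The documents give no value; 10%, 20% and 30% are assumptions. For a rate p in the remaining patients, the arm rate is f + (1 − f)p, so every difference between arms is multiplied by (1 − f).

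**3. Non-inferiority.** Suppose that in the remaining patients individual therapy gives 57% and group therapy 42%, a 15-point deficit. With 135 per arm and clustering ignored,

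P(declare non-inferiority) = Φ[(0.15 − d)/SE − 1.645], where d is the difference among all enrolled patients.

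| f | Individual | Group | d (points) | SE | P(declare) |
|---|---|---|---|---|---|
| 0 | 57.0% | 42.0% | 15.0 | – | 5.0% |
| 10% | 61.3% | 47.8% | 13.5 | 0.0600 | 8.2% |
| 20% | 65.6% | 53.6% | 12.0 | 0.0593 | 12.7% |
| 30% | 69.9% | 59.4% | 10.5 | 0.0578 | 19.3% |

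Worked line for f = 20%: SE = √[(0.656 × 0.344 + 0.536 × 0.464)/135] = 0.0593; 0.030/0.0593 = 0.506; Φ(0.506 − 1.645) = 0.127.

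If the overall individual rate is instead held at 57%, so that f already sits inside it, the probabilities are 8.1%, 12.5% and 18.4%. The result hardly depends on that choice. Read the other way, a 15-point margin among all enrolled patients tolerates 15/(1 − f) = 16.7, 18.8 or 21.4 points among the remaining ones.

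**4. Superiority.** The planned contrast is 57 − 25 = 32 points. If f comes on top of both rates, it becomes 28.8, 25.6 and 22.4 points. With 48 control and 135 group-hypnotherapy patients evaluable (54 and 150 less 10%), power falls from 98% at f = 0 to 94%, 87.5% and 79%. With the design effect 1 + 5 × 0.05 = 1.25, it falls from 95% to 88%, 79% and 70%. If f is already part of the 25% and the 57%, the contrast stays at 32 points.

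**The case against.** A reader might infer that the plan inflates the type I error, with a false non-inferiority claim in 8% to 19% of trials. The documents do not support that. The margin in Sample Size Calculation refers to the response difference between the two hypnotherapy arms as enrolled. The enrolled differences of 13.5, 12.0 and 10.5 points all lie inside 15, so declaring non-inferiority there is correct by the plan's own definition. The error rate at a true 15-point difference among enrolled patients stays at 5%.

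Other objections also stand, in whole or in part:

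- **f has no source and may be small.** Patients are referred, are described as motivated, and accept six sessions with daily homework. Three pain days in one week is the extreme of eligibility, and a week without pain need not be answered as a week with adequate relief.
- **Double counting.** Patients who respond regardless may already be part of the assumed 25% control response, which would reduce or remove the dilution of the superiority contrast.
- **Broad entry is deliberate.** Selection of the study population argues for heterogeneity and generalisability, and the 2-days-a-week figure is a recommendation, not a requirement. Leaving it out is not a contradiction.
- **Partial information exists.** The week 0 IBS module and the IBS-SSS, which covers pain severity and frequency, can describe patients with infrequent pain. They do not record the endpoint itself.
- **Screening on one answer would not work.** A single negative answer about the past week would admit the episodic patient asked in a bad week. It would also select patients at a low point.

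The objections do not remove the core point. A responder state scored without a baseline cannot separate improvement from mild or episodic disease at entry, and no later analysis can recover an answer that was never collected. Adjustment for confounders does not help either, because it is triggered by differences between arms and these patients are expected to be balanced.

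**Conclusion.** The point holds as a loss of assay sensitivity. It matters most for group versus individual hypnotherapy, where dilution favours the hoped-for conclusion; superiority is fairly robust unless f is large. The size is unknown. The illustration of 13.5 to 10.5 points and 8% to 19% rests on an assumed f of 10% to 30%, on those patients responding in every arm, and on a 15-point deficit confined to the rest. If some of them lose relief during the trial, the dilution is smaller. Under the present schedule the report could give no direct estimate of f.

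**What to change.** 1. Add the adequate-relief question before treatment, preferably weekly over the four weeks before the first session so that it matches the endpoint, otherwise once at week 0. Collect it before patients learn their arm where possible; the week 0 questionnaires are already completed before randomisation.
2. Adjust both primary comparisons for baseline relief and baseline IBS-SSS, and still report a difference in percentage points, because the margin is on that scale.
3. Prespecify a repeat of both comparisons, above all non-inferiority, in patients without adequate relief at baseline. Repeat them also in patients who meet the 2-days-a-week threshold, as far as the week 0 IBS module or the IBS-SSS pain-frequency item shows it.
4. State whether the threshold quoted in the Background applies to entry. Broad entry can stay.

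**Cost.** One short extra questionnaire and no loss of recruitment. Enrolment began in May 2011, so patients already treated can be classified only from the week 0 module and IBS-SSS. The restricted repeat is less precise: at f = 20% it has 0.8 × 135 = 108 per arm, SE = √(2 × 0.57 × 0.43/108) = 0.067, and power Φ(0.15/0.0674 − 1.645), about 72%, if both arms respond at 57%. It therefore serves as a sensitivity analysis, not as a replacement for the primary one.
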